## Materials and methods

### Empathy elicitation using VR

Based on the narrative review on the use of VR for eliciting empathy [1], we have decided to immerse participants in 360º and three-dimensional (3D) virtual environment due to VR’s efficacy in eliciting empathic responses. Our choice of a 360º immersive setting is substantiated by comparative analyses demonstrating that it is equally or more effective at eliciting empathy compared to other approaches such as two-dimensional video/film [1, 34, 35], curriculum contents like workshops [36] or e-course materials [37], narrative-based perspective-taking exercises [9, 38], and text-based information [9, 35]. This effectiveness is observed immediately or with a lasting positive impact. Additionally, our decision to utilize a 3D level of immersion aligns with the findings of the review [1], which highlight the superior effectiveness of 3D immersion over two-dimensional.

During the VR experience, participants will adopt a first-person perspective, allowing them to observe the actors expressing emotions directly in front of them. This approach was chosen because research suggests that a first-person perspective is more effective than a third-person perspective, where the participant merely observes events happening among others [39, 40].

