### VR sessions

The sessions, conducted with and without narratives, are structured in the following manner:

With narratives:
In preparation for the session, the participants will be requested to fill out questionnaires pertaining to personal information, including age, gender, health status, proficiency in the Slovenian language, prior experiences with VR, employment or study status, field of work or study, and educational background. This questionnaire, developed by our team, is provided in S5 Appendix. Additionally, participants will be asked to complete the Questionnaire of Cognitive and Affective Empathy (QCAE) [3] to assess their trait empathy. Trait empathy represents the individual’s innate capacity for empathetic behavior and is closely linked to personal characteristics [42].The first step of the VR session is calibration. To calibrate the baseline, participants will be asked to relax, breathe normally, and avoid facial expressions and head movements during a 2-minute recording. They will later be prompted to perform several voluntary facial expressions. The data recorded during these voluntary facial expressions will inform the subject-specific normalization of EMG signals, following the approach suggested in certain studies [43–45].Following the calibration process, participants will be exposed to a 2-minute forest video. Its purpose is to establish a baseline, reflecting the participants’ relaxed state. The forest video utilized in this study was an existing video titled ‘The Amsterdam Forest in Springtime,’ sourced from YouTube.Subsequently, the main segment of the session entails the four sets of narrative-video pairs. Each pair consists of the emotional narrative read by the corresponding actor, followed by the video portraying the actor expressing the specific emotion. The emotions portrayed in these pairs include anger, sadness, happiness, and anxiousness. The duration of each narrative-video combination ranges from 2 to 3 minutes. The participants will be instructed to empathize with the individuals in the video recordings.Following the observation of each narrative-video pair, participants will provide brief feedback on their current empathic state. They will do so by answering three out of the four different items that measure affective empathy from the 12-item State Empathy Scale developed by Lijiang Shen, based on the Interpersonal Reactivity Index (IRI). The selection of these three questions specifically is made because factor analysis requires at least three indicators or items per factor. We have excluded the first item in this scale as it appears to assess the quality of the actor’s performance rather than empathy. Therefore, we specifically utilized the 2nd, 3rd, and 4th items before moving on to the next pair [46]. State empathy refers to the temporary affective response evoked in specific situations [47]. This procedure will be repeated four times, with each iteration featuring a distinct emotion. The duration of each empathic state report is expected to be up to 30 seconds.In addition to the state empathy questions, participants will be requested to provide brief feedback on their current arousal and valence states using the arousal and valence statements from the self-assessment manikin (SAM) affective rating system [48]. This inclusion of arousal and valence measures alongside state empathy is crucial because it offers a more comprehensive insight into emotional experiences during VR sessions. Arousal and valence are fundamental components of emotional responses and are often intertwined with empathy [49].After the participants provided brief feedback on their current arousal and valence states, we included one item to assess personal distress, specifically question number 17 from the personal distress items based on the IRI [15].The final segment of the session involves a roller coaster video titled ‘Official 360 POV—Yukon Striker—Canada’s Wonderland’, which was sourced from YouTube. This video, as a control measure were implemented, to address potential confounding variables, particularly to differentiate between non-empathic psychological arousal and the empathic arousal expected from the main video. While the primary response stimuli consisted of videos designed to evoke empathic physiological arousal, a control stimulus, namely a roller coaster video, was incorporated to induce non-empathic arousal. We believe that this strategic control will facilitate the differentiation between empathic and non-empathic responses, enhancing the validity and reliability of the study’s findings. One of our experiments aims to examine the differences in physiological responses between empathically stimulating content and non-empathic, arousal-inducing content, such as the roller coaster video.The session’s final segment is followed by the arousal and valence statements from the SAM affective rating system [48], with the aim of comparing the intensity of arousal and valence after the roller coaster video and arousal, valence and empathic states following each pair of narrative-video.At the conclusion of the session, we will administer a presence questionnaire adapted from the Bongiovi Report [50]. The questionnaire has been modified to include questions from the presence section, as well as an additional inquiry regarding any challenges encountered by participants that may have hindered their VR experience (refer to S6 Appendix).Without narratives:

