### Data collection

Data from the participants will be collected using two devices: the emteqPRO system and the Empatica E4 wristband. The emteqPRO system consists of a sensing mask attached to the Pico Neo 3 Pro Eye VR headset (Fig 2). It includes features such as EMG to measure facial muscle activation (expressivity), photoplethysmography (PPG) for heart-beat monitoring, inertial measurement unit (IMU) to track head motion, and eye tracking to observe eye movements and objects of interest. The Empatica E4 wristband includes an electrodermal activity (EDA) sensor (galvanic skin response), an infrared thermopile that reads peripheral skin temperature, a 3-axis accelerometer that captures motion-based activity and a PPG sensor [43]. Both devices are equipped with an internal clock [52, 53].

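### The roller coaster control differs from the actor clips in more than empathy, so the ride-versus-clip contrast cannot by itself show that a physiological response is specific to empathy

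*Protocol article*

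**What the plan says.** The protocol article, VR sessions, ends each session with a roller coaster video. It calls the video a control for confounding, included "to differentiate between non-empathic psychological arousal and the empathic arousal expected from the main video". It adds that "a control stimulus, namely a roller coaster video, was incorporated to induce non-empathic arousal", and the authors believe that "this strategic control will facilitate the differentiation between empathic and non-empathic responses, enhancing the validity and reliability of the study’s findings". One planned experiment is to "examine the differences in physiological responses between empathically stimulating content and non-empathic, arousal-inducing content, such as the roller coaster video".

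The title of the ride video contains "Official 360 POV", so it is shown from the rider's viewpoint. In the emotion clips the first-person set-up differs: Empathy elicitation using VR describes it as "allowing them to observe the actors expressing emotions directly in front of them". VR sessions adds that participants are told to empathise with the people shown.

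SAM arousal and valence are rated after each emotion clip and again after the ride. State empathy is rated after each clip; no state-empathy items are listed after the ride. The recorded channels include the "inertial measurement unit (IMU) to track head motion, and eye tracking to observe eye movements and objects of interest" (Data collection), a wrist accelerometer, facial electromyography (EMG), pulse signals (PPG) and skin conductance. Strengths and limitations does not discuss what the ride can and cannot control for.

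**The concern.** A control meant to isolate empathy should resemble the main stimulus in everything that moves the measured signals, apart from empathy. This control departs from the clips in several such respects at once. A physiological difference between ride and clips then has several sufficient explanations, and empathy is only one of them.

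What is at stake is the specificity claim: that the recorded response to the clips is empathic and not arousal in general. Read as the article proposes, a positive contrast would be reported as supporting that claim, although much the same result would be expected if the clips evoked no empathy at all. The article itself names sensitivity to non-empathic influences as a weakness of psychophysiological measures (Introduction), and this control is its stated answer to that weakness.

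**Working it through.** The article gives no figure for this contrast, so there is none to reproduce. The check sets the two stimuli side by side and asks which differences the planned measures could separate.

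| Feature | Emotion clips | Ride video |
|---|---|---|
| Apparent self-motion | None described; the viewer observes an actor in front | Implied by a point-of-view roller coaster |
| Expressive person facing the viewer | Yes | None described; inferred from the title and the non-empathic label |
| Instruction to empathise | Given | None described |
| Self-report afterwards | State empathy, SAM arousal and valence, one distress item | SAM arousal and valence |

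**Step 1: what the contrast contains.** As a simple additive sketch, write the mean physiological difference as

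D = E + M + P + I + A,

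where E is empathic response, M self-motion, P presence of an expressive person, I the instruction, and A a difference in the amount of arousal. The design supplies one contrast for five unknowns. With E = 0, D is still nonzero unless M, P, I and A happen to cancel.

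**Step 2: which channels are exposed.** Head motion (the inertial sensor and the derived head-activity feature) and gaze can be expected to follow scene content. The wrist accelerometer records the wearer's own movement, so it is affected only if the ride makes participants move or brace. The derived arousal and valence features come from EMG and PPG (Data collection), which facial tension and movement can also affect. So at least two channels, and plausibly more, can differ without empathy.

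**Step 3: what existing measures can remove.** SAM ratings bear on A as reported by the participant. They do not remove M, P or I. Leaving out motion and gaze features reduces M in part. The forest video is a relaxed baseline, so it does not match the clips on arousal. Because state empathy is not listed after the ride, the label non-empathic is assumed and not checked.

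**Step 4: what the clips offer instead.** Among the clips, the type of stimulus, the facing actor and the instruction are shared, so M, P and I are broadly held constant while reported empathy varies. State empathy, SAM arousal and SAM valence are all collected after each of four emotions. With about 100 participants that gives 4 × 100 = 400 clip-level records, clustered within participants, each with the ratings needed for an adjusted analysis.

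The ride also always comes last ("The final segment of the session involves a roller coaster video titled"), which adds a difference in position. The point does not rest on that.

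**The case against.** **The missing empathy target is the manipulation.** A non-empathic control has to lack someone to empathise with. This stands in part, and for that reason person presence is the weaker leg. It still cannot be told apart from empathy in this contrast, and self-motion is not part of the intended manipulation and is sufficient alone.

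**The ride's content is inferred.** This also stands. The article gives only the title, and other riders may be visible. Apparent self-motion follows from a point-of-view coaster; the absence of a person does not follow with certainty.

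**The contrast is peripheral, and the claim is cautious.** The ride comparison is one experiment among several. It does not appear among the research questions in Data analysis or the aims in Discussion, and the authors express a belief that the control will help. This limits the scope but does not repair the inference.

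**Much of the remedy is already there.** Relating state empathy to physiology is the core analysis, and arousal and valence ratings are among the listed features. That is fair; explicit adjustment for this purpose and a restricted reading of the ride contrast are what is new.

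Some stronger readings are tempting but not supported:

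- A reader might infer that SAM ratings serve only to compare intensities, or that the physiological contrast is left unadjusted. Data collection and Data analysis make questionnaire data, including the post-ride ratings, analysis inputs. The model for this contrast is not given, and an article may leave that to a fuller document.
- A reader might infer that a classifier will be trained to tell ride from clip. The labels in Data analysis are trait and state empathy only.
- A reader might infer that the prediction model is undermined. It predicts empathy scores and does not depend on the ride contrast.
- A reader might treat the neutral phases of the clips as a ready-made better control. They are described only for the version without narrative, one of five, and the return to neutral directly follows peak emotion, so carry-over is possible.

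**Conclusion.** The concern holds for the ride-versus-clip comparison. That comparison cannot by itself distinguish empathic from non-empathic arousal, because self-motion, person presence and the instruction to empathise change together with empathy. Strengths and limitations does not say so.

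The size of the bias is not computable from the article. The expectation of a difference without empathy is reasoned, not calculated. It assumes that the ride produces apparent self-motion, as its title implies, and that head motion and gaze respond to it. It does not need the assumption that no person is visible in the ride.

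The consequence is an over-strong interpretation of a secondary comparison. The change is worth making because it is cheap, but the main association and prediction aims do not depend on it.

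**What to change.** 1. Take the specificity evidence from within the emotion clips. Test the association of post-clip state empathy with each physiological response, first unadjusted and then adjusted for SAM arousal and valence from the same clip. Account for the repeated clips per participant, for example with a participant random effect. Report both estimates.
2. Keep the ride contrast as a secondary check. Report it with and without head-motion, accelerometer and gaze features, and with adjustment for SAM arousal. Describe it as ride versus actor content, not as empathic versus non-empathic arousal.
3. State in Strengths and limitations that self-motion and person presence are not separated from empathy in this contrast.

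**Cost.** No new measures are needed: state empathy and both SAM ratings are already planned after every clip, and SAM after the ride. The article itself regards arousal and valence as often intertwined with empathy, so adjustment loses some precision and may remove part of the empathic signal. The adjusted estimate should therefore not replace the unadjusted one. The ride contrast remains confounded after step 2, since neither restricting features nor adjusting for SAM removes person presence or the instruction.

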blood volume pulse (BVP) obtained from the PPG signal;average heart rate extracted from the BVP signal;fluctuations in specific electrical properties of the skin, gained from the EDA sensor;motion-based activity obtained from the 3-axis accelerometer;peripheral skin temperature, captured through the infrared thermopile;time between individual heart beats extracted from the BVP signal.

In addition to the sensor data, our analysis will incorporate features obtained from the mentioned questionnaires. These include the personal information questionnaire, the trait empathy questionnaire, the presence questionnaire, the arousal and valence questions after the roller coaster video, and the state empathy, arousal and valence questions asked four times, because the participants will be instructed to regularly report their empathy towards the actors after each emotion expressed in the video session.

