### Data analysis

In order to process the collected data effectively, several steps will be taken. Firstly, the derived features obtained from each module of the Emteq Emotion AI Engine, as well as the features from the Empatica E4, will be combined by concatenating the data files. The epoch timestamps will then be converted to human-readable date and time formats, and the output labels will be populated based on the scores from the empathy questionnaires. The classification task will involve multi-label classification, with the affective component of trait empathy and state empathy serving as the labels of interest.

If a variable has a modest amount of missing values, imputation will be used. Otherwise, if the amount is substantial, the corresponding data will be dropped. The derived features are provided by different devices with data updated at different intervals, ranging from 10 seconds to 500 milliseconds, resulting in varying data frequencies. Undersampling or oversampling will be used to handle the high or the low frequency of the derived features accordingly, and they will be aligned at a consistent interval. Regarding the variables, while some are ready to be used, as the derived features are, from others, such as the raw sensor data, we will extract features.

The research aims to address several key questions. Firstly, it seeks to explore the connection between physiological attributes and empathy. For this purpose we will use multiple standard machine learning classifiers to develop prediction models, with different parameters tested to optimize performance. The predictive models will be developed based on the descriptive space consisting of physiological data from the sensors and data from the questionnaires. Additionally, personalized models will be explored to enhance predictions. Personalized feature values will be utilized, employing normalization techniques by calculating the ratio between the parameter value and the average value for each participant over the entire viewing period. If the initial results prove unsatisfactory, deep learning techniques will be applied directly to the raw sensor data, bypassing the use of the derived features provided by Emteq. Furthermore, we will explore deep learning approaches using the derived features, allowing us to consider both options.

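### The roller-coaster control carries no state-empathy score, and its planned uses do not test whether the state-empathy model separates empathy from arousal

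*Protocol article*

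**What the plan says.** The VR sessions section adds the roller-coaster video as a control for confounding, "particularly to differentiate between non-empathic psychological arousal and the empathic arousal expected from the main video". It expects a benefit for the whole study: "We believe that this strategic control will facilitate the differentiation between empathic and non-empathic responses, enhancing the validity and reliability of the study’s findings".

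Two uses are stated there. One is an experiment on how physiological responses differ between empathic content and content that is arousing but not empathic. The other is "comparing the intensity of arousal and valence after the roller coaster video and arousal, valence and empathic states following each pair of narrative-video".

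For the three state-empathy items, the same section says: "This procedure will be repeated four times, with each iteration featuring a distinct emotion". After the roller coaster it lists only the arousal and valence statements. The Data collection section agrees, naming "the arousal and valence questions after the roller coaster video, and the state empathy, arousal and valence questions asked four times".

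In Data analysis, "the output labels will be populated based on the scores from the empathy questionnaires", "with the affective component of trait empathy and state empathy serving as the labels of interest". Trait empathy comes from a questionnaire completed once, before the session. The predictors are sensor data and questionnaire data.

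**The concern.** The product promised in the Introduction is a model that measures empathy directly from physiological signals, and the Discussion speaks of a reference standard. Many inputs respond to arousal of any kind: four derived arousal features, seven heart-rate-variability features and electrodermal activity. The protocol recognises the problem. It lists sensitivity to factors other than empathy among the limits of psychophysiological measures, and it describes arousal and valence as often bound up with empathy.

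The roller coaster is the one stimulus included to separate the two. If it is not brought to bear on the fitted model, good performance on the emotion clips has two explanations, a signal of empathy or a signal of arousal that goes along with it. The headline claim needs the first.

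**Working it through.** The protocol gives no figure on this point, so there is none to reproduce. The check is a count of labels, a look at what each planned use can show, and an illustration with assumed inputs.

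**1. Labelled segments.** Inputs: about 100 participants (Strengths and limitations); four state-empathy ratings and one roller-coaster segment each (VR sessions); labels taken from the empathy questionnaires (Data analysis).

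| Segment | Number | With state label | With trait label |
|---|---|---|---|
| Emotion clips | 4 × 100 = 400 | 400 | 400 |
| Roller coaster | 1 × 100 = 100 | 0 | 100 |
| All | 500 | 400 | 500 |

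For the state-empathy model the control supplies 0 of 100 labelled cases. The trait label can attach to all 100, but its value is the same for a person's four clips and for that person's coaster segment. The within-person difference in label is therefore zero, and it says nothing about whether a given arousal was empathic.

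**2. What the stated uses can show.**
- *Physiological comparison.* This can show that the two kinds of content produce different signals. They also differ in content and apparent self-motion, and head activity and wrist acceleration are among the recorded variables. A difference could arise without any empathy signal, and the fitted model is not involved.
- *Comparison of ratings.* This sets self-reports side by side. The model is again not involved.
- *Coaster ratings as features, and normalisation over the whole viewing period.* These make the segment an input or part of a denominator. Neither is a test.

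**3. Illustration.** The protocol gives neither the correlation r between arousal and state empathy within the emotion clips nor the arousal difference between coaster and clips; both are assumed here. Take bivariate normal scores, a high/low label split at the median of empathy, and a rule that uses arousal alone, split at its own median.

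- Accuracy = 1/2 + arcsin(r)/π
- AUC = 1/2 + (2/π)·arcsin(r/√2)

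| Assumed r | Accuracy | AUC |
|---|---|---|
| 0 | 0.50 | 0.50 |
| 0.3 | 0.60 | 0.64 |
| 0.5 | 0.67 | 0.73 |
| 0.7 | 0.75 | 0.83 |

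Example, r = 0.5: accuracy = 0.5 + 0.5236/3.1416 = 0.667; AUC = 0.5 + 0.6366 × 0.3614 = 0.730. A simulation of 400,000 draws gave the same values to within 0.001.

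If coaster arousal has the same spread as clip arousal but a mean s SD higher, the same rule calls a share Φ(s) of coaster segments high empathy: 69% for s = 0.5, 84% for s = 1.0 and 93% for s = 1.5. This share does not depend on r, and the clip results do not depend on s. Clip performance therefore cannot reveal the coaster result.

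**The case against.** Several objections have weight.

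- **A reader might infer that the label rule shuts the roller coaster out of all models.** It does not. The trait label can attach to any segment, the coaster's arousal and valence ratings are listed as features, and the normalisation window read literally includes the segment. No text excludes it. The point is limited to the state-empathy label.
- **A reader might see a contradiction in the planned comparison with empathic states.** The sentence lists only arousal and valence on the coaster side and promises no empathy score there. Participants rate empathy towards the actors, so leaving out that rating on a ride is consistent with the design.
- **The control has stated uses, and the stated aim is to tell kinds of response apart, not to estimate the specificity of a model.** This is fair. But the benefit is claimed for the validity of the study's findings, and the main outcome is the model.
- **The article is condensed, and validation detail may sit elsewhere.** This also stands, so it cannot be said that the model will never be tested against the control. The point rests on what is fixed here: which ratings are taken, where labels come from, and the uses that are stated.
- **That the model is an arousal detector is not shown.** Correct. At r = 0 the arousal-only rule does no better than chance. Arousal is also rated after every emotion clip, so the data for a check on the labelled clips exist.

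**Conclusion.** The point holds in a limited form. The control meant to separate non-empathic from empathic arousal has no state-empathy score, so it cannot be a labelled case for the state-empathy model (0 of about 100 segments). The trait label cannot do the separating, because it does not vary within a person. The stated comparisons do not involve the fitted model. It follows that performance on the four emotion clips alone could not rule out a state-empathy model that largely tracks arousal.

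The size of that risk is unknown. It runs from none (AUC 0.50) to substantial (AUC 0.83) over assumed correlations of 0 to 0.7, and the coaster shares of 69% to 93% also rest on assumed shifts. The label count needs only the stated procedure and the approximate sample size.

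The change is worth making because it is cheap and uses a segment recorded in every participant. It is not a reason to doubt the data collection as such.

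**What to change.** Add two analyses to the Data analysis section, with each participant kept wholly in either the fitting set or the test set.

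1. **Arousal-only comparator.** On held-out emotion clips, compare the state-empathy model with a model that uses only self-rated arousal and the derived arousal features. Report the gain.
2. **Roller coaster as negative control.** Apply the fitted state-empathy model unchanged to the coaster segments of held-out participants. Because the protocol defines this stimulus as non-empathic, no empathy rating is needed. Leave the coaster out of the normalisation average, and leave out of the model any questionnaire input not recorded for that segment. Report the predicted scores beside those for the same participants' actor clips with similar self-rated arousal, with and without the head-activity and accelerometer features.

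Treat the result as supportive evidence on specificity, not as a pass/fail rule. There is one control stimulus, it always comes last, and it differs from the clips in content and self-motion, so applying the model to it is an extrapolation. If coaster predictions are as high as those for arousal-similar clips, or there is no gain over the arousal-only model, do not claim that the model measures empathy separately from arousal.

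Cost: a little more analysis and text, with no new data, participants or procedures. The downside is that the headline claim may weaken.
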